# Selection and withdrawal of subjects

### 4.1 Inclusion criteria

Patients:

- 75 years of age or older

- male or female

- admitted to the traumatology ward (E456) with an osteoporotic fracture

- Proximal femoral fracture
- Proximal humeral fracture
- Fracture of the pelvis / acetabulum
- Fracture of the thoracic/lumbar vertebrae (multiple fractures are allowed)
- Fracture of the wrist

- ability of the patient or assigned representative to understand the content of the patient informed consent form (see **appendix 2** for the pre-post cohort and **appendix 2.1** for the feasibility study).

- signed and dated informed consent.

Health care professionals:

- Working on E456

- Had four or more weeks of ‘full time’ experience with the program.

### 4.2 Exclusion criteria

- patient in palliative care setting not expected to live longer than 3 months.

- multi-trauma injuries except for presence of multiple vertebral fractures

- patient or assigned representative are unable to speak and/or understand Dutch

- periprosthetic fracture

- concomitant joint-infection

- admission from another hospital or hospital unit (reason: no full baseline data on premorbid conditions such as mobility, functional status, … available)

### 4.3 Expected duration of trial

Start Oct 2021 with inclusions of first patients in pre-cohort, till March 2022 with 1 year follow-up. Patients in the feasibility study will be recruited before start of the post-cohort and will start whenever the project team is convinced that the G-COMAN program is implemented as wanted. This will preferably be in the timeframe between May - July 2022. Post- cohort patients will be recruited from Sept 2022 onwards to Sept 2023 with again 1 year follow-up

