Combining the successful results of G-COACH and the orthogeriatric care model abroad, we set up a care strategic project (2021-2024) for geriatric-surgical co-management within the University Hospitals Leuven, named **G-COMAN**. G-COMAN aims to optimize geriatric care in elderly surgical patients through a phased implementation of geriatric surgical co-management on the services traumatology, abdominal surgery and vascular surgery. This year (2021) is dedicated to pre-implementation. From 2022 onwards, G-COMAN will start implementing the program on the traumatology ward. Dedicated nurses will perform comprehensive geriatric assessments (CGA) in all patients aged 75 and older on the traumatology ward. By systematically organizing proactive care with collaboration and shared decision making between geriatric and surgical departments, postoperative care outcomes will hopefully improve.

This observational study will evaluate the **effectiveness of geriatric-traumatology** part of the G-COMAN program and will examine **which factors contribute to** a (non)successful **implementation** of the program as we aim to sustainable embed geriatric care aspects in the standard care of surgical services.

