### 3.4 Trial Design

single-centre pre-post implementation study on the traumatology ward of the University Hospitals Leuven

**Usual care (pre-cohort):** the control group receives usual care on the traumato ward. This means that the patient is cared for by a surgical resident. The interprofessional team furthermore consists of ward nurses, a physiotherapist, an occupational therapist and a social worker. No tailored geriatric protocols are available to the traumato team, except for those that are available hospital-wide for all patients (e.g. fall prevention, delirium). Geriatric expertise is available upon active request by the traumato team and includes the comprehensive evaluation of the patient by a geriatric nurse (consultation model).

Due to the design of the G-COMAN strategic project and its predefined strict timing schedule (a phased implementation with the need of a rapidly full implementation), the timeframe for inclusion of the pre-cohort is limited. At the end of the pre-cohort, the predefined sample size will not be reached. To obtain sufficient included patients in the pre-cohort, this patient cohort will be supplemented with patients of which retrospectively information will be gathered. This results in a pre-cohort that will be partly prospective and partly retrospective.

**Geriatric co-management intervention, quality-improvement project G-COMAN (post-cohort):** A dedicated traumato nurse (G-COMAN nurse) will systematically perform a frailty screening in all newly admitted older patients on the traumato ward to evaluate if they are to be included in the G-COMAN program. In eligible patients, a comprehensive geriatric assessment (CGA) will be performed by the G-COMAN nurse. Based on identified potential problems, a tailored care plan based on predefined geriatric protocols will be launched. As part of the project a geriatric specialist nurse will provide every weekday training and education of the G-COMAN nurse and other team members on the traumato ward. The implementation of automated care plans and predefined geriatric protocols will be coordinated by a G-COMAN project coordinator, as well as the organisation of focus groups and intervisions to ensure smooth and supported collaboration.

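### Prospective controls are admitted only in October–March and the post-cohort over a full year, and neither the undated retrospective supplement nor the 8.2 covariates deal with season

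*Protocol*

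**What the plan says.** Section 4.3 gives the recruitment windows. The pre-cohort line reads "Start Oct 2021 with inclusions of first patients in pre-cohort, till March 2022 with 1 year follow-up". For the post-cohort, "cohort patients will be recruited from Sept 2022 onwards to Sept 2023 with again 1 year follow-up".

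Section 3.4 accepts that the prospective controls will fall short of the sample size, so "this patient cohort will be supplemented with patients of which retrospectively information will be gathered". It gives no admission period, no rule for selecting consecutive patients and no matching on calendar month.

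Section 3.2 lists pneumonia among the six items of the primary endpoint. The multivariable model in 8.2 adjusts for age, gender, Katz, Parker score, grip strength, Mini-Cog, Charlson and MNA. It has no term for season or calendar time. The end of 8.2 acknowledges bias from lack of randomisation, but only in general terms.

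On timing, Background and rationale says "This year (2021) is dedicated to pre-implementation" and then "From 2022 onwards, G-COMAN will start implementing the program on the traumatology ward", with no month. Section 3.4 says that "the control group receives usual care on the traumato ward". Of the feasibility study, which precedes the post-cohort, 4.3 says "This will preferably be in the timeframe between May - July 2022".

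**The concern.** In a before–after comparison, anything that differs between the two periods is carried into the estimated effect unless the design balances it or the analysis adjusts for it. Season of admission differs here between the prospective controls and the post-cohort. The retrospective patients could correct this or leave it, depending on when they were admitted, and the plan does not say when.

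If complications are more frequent in winter, a control group weighted towards winter makes the programme look better than it is. The headline t-test in 8.2 is unadjusted, and the adjusted model has no seasonal term, so neither analysis would remove the difference.

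The go-live date is a second, separate matter. Section 3.4 describes training of the ward team, so an early roll-out could reach patients counted as usual care. That would shrink the observed difference, which is dilution rather than confounding.

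**Working it through.** **The plan's own figure.** Section 8.1 gives 108 per group for a 20-point reduction, two-sided alpha 0.05, power 0.80 and 5% loss. The two-means formula with SD 0.5 gives 99, and 99/0.95 = 105. Two proportions with continuity correction, 71% against 51%, give 102, and 102/0.95 = 108. The figure is reproducible and is not in dispute. Below I use 102 evaluable patients per group (108 × 0.95 = 102.6).

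**Season: shares from 4.3, assuming even accrual by month**
- Prospective pre-cohort: 6 of 6 months are October–March, so 100%.
- Post-cohort: 6/12 = 50%, or 6/13 = 46% if both Septembers count in full.
- Full pre-cohort: unknown, because the retrospective window is undated.

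Spurious benefit = d × (w_pre − w_post), where d is the winter-minus-summer difference in rate and w is the October–March share.

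The protocol gives no seasonal rates, so d is assumed. The table uses w_post = 0.50.

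| Assumed pneumonia rate, Oct–Mar / Apr–Sep | d | All controls Oct–Mar (w_pre = 1) | Half retrospective and season-balanced (w_pre = 0.75) |
|---|---|---|---|
| 10% / 7% | 3 | 3 × 0.50 = 1.5 points | 3 × 0.25 = 0.75 points |
| 12% / 6% | 6 | 3.0 points | 1.5 points |
| 15% / 8% | 7 | 3.5 points | 1.75 points |

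With w_post = 6/13, the first set of results becomes 3 × 7/13 = 1.6, 6 × 7/13 = 3.2 and 7 × 7/13 = 3.8 points.

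If the retrospective half were all April–September, w_pre = 0.50 and the bias is zero. If April–September patients made up more than half of all controls, its sign would reverse.

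If d is instead taken for complications overall, assumed values of 2, 5 and 10 points give 1.0–1.1, 2.5–2.7 and 5.0–5.4 points when all controls are October–March. At an assumed 60% control rate with no true effect, a spurious 2.5 points gives a 5.5% chance of a significant result favouring the programme, and 5 points gives 10.8%. The nominal one-sided rate is 2.5%.

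**Possible overlap with implementation.** At most January–March 2022 is exposed, which is 3 of the 6 prospective months. This requires a 1 January start, which the protocol does not state.

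Observed effect = 20 − (share of controls exposed) × (fraction of effect received) × 20. Power is for an assumed 60% against 40%.

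| Share of controls exposed | Fraction of effect | Observed effect | Power |
|---|---|---|---|
| 0 | – | 20 points | 0.82 |
| 0.25 (half the controls retrospective) | 0.5 | 17.5 points | 0.71 |
| 0.50 (no retrospective controls) | 0.5 | 15 points | 0.57 |
| 0.25 | 1.0 | 15 points | 0.57 |
| 0.50 | 1.0 | 10 points | 0.30 |

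**The case against.** **Season.** A reader might infer that season is built into the group contrast. The document does not support that. The control group to be analysed is prospective plus retrospective patients, and the retrospective part may balance the months. What stands is that nothing in the plan makes it do so. The seasonal rates are also assumptions. If the endpoint is read as any complication, pneumonia points do not carry over one for one, because some of those patients have another listed complication anyway. The effect is modest against a 20-point target.

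**Overlap.** A reader might also infer that controls were enrolled after implementation began. This is not shown. The 2022 start in Background and rationale carries no month, and a start after March fits it. Section 3.4 defines the pre-cohort as usual care, and its limited window is attributed to the implementation schedule, which suggests that recruitment closed to make way. The order in 4.3 (pre-cohort, feasibility, post-cohort) fits that reading too. What stands is that no date rules overlap out. The larger losses in the second table need an early start and an immediate effect, so they are worst cases.

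**Remedy.** Drawing the retrospective patients from April–September alone would make almost all summer controls record-based and all winter controls prospective. Season would then be nearly inseparable from ascertainment method within the pre-cohort. That objection is sound and shapes the fix. Closing the pre-cohort earlier is no longer possible, since this version is dated 22-04-2022, after the March 2022 close.

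**Conclusion.** The concern holds in a limited form. Prospective controls are October–March only, the post-cohort spans a year, the retrospective window is open, and the 8.2 model has no seasonal term. Followed as written, the plan neither guarantees seasonal balance nor adjusts for its absence.

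The size cannot be derived from the protocol. On the assumed pneumonia rates it is at most about 1.5–3.5 points if every control were an October–March admission, and about half that if half the controls are retrospective and season-balanced. It could be nil with a suitable window. Other components that vary by season would add to it.

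Overlap with implementation is possible but unproven. If it occurred, it would pull the estimate towards no effect. With higher winter complication rates the two act in opposite directions, and their net direction is unknown.

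**What to change.** 1. **8.2:** add season of admission (October–March or April–September) to the multivariable model. Admission date is already collected under 5.1. The post-cohort covers both seasons, so the term can be estimated.
2. **3.4 and 4.3:** define the retrospective window as consecutive admissions before go-live, chosen so that the whole pre-cohort covers the same calendar months as the post-cohort. This also protects the unadjusted comparison, which a model term cannot do. Preferably include some October–March admissions, so that season and data source are not fully aligned.
3. **Background and rationale, 3.4 and 4.3:** state the ward go-live date and reconcile the three sections. Replace any control admitted after that date with a retrospective one, or exclude such controls in a sensitivity analysis.

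The cost is one extra model term and some wording, since retrospective patients are being added anyway. Season remains partly aligned with record-based ascertainment within the pre-cohort, so its effect is estimated mainly from the post-cohort and is assumed to be the same in both periods. Using earlier years brings some secular drift, and the written-consent condition under Quality assurance has to be met for those patients as well.

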# Trial Procedures

### 5.1 By visit

### Baseline assessment

All patients who were screened for the inclusion and exclusion criteria will be entered on the ‘Subject screening log’ (see appendix 1). **Demographical data** (gender, age, height and weight (to calculate the Body Mass Index), date of admission and living situation), American Society of Anaesthesiologists (ASA) physical status class^15^, comorbidities (age adjusted charlson comorbidity Index (ACCI) will be all collected by reviewing the patients’ medical record. **Functionality** (Parker Mobility Score, modified Barthel Index, Lawton and Brody Scale, Katz index), **quality of life** (EQ-5D), **fall history and residential status** will be assessed referring to the patient’s pre-injury status. **Mental status**, based on cognition, and **nutritional status** will be assessed with respectively Mini-cog and mini nutritional assessment. Details relative to the **injury** (side affected, fracture location, fracture classification), **surgery** (time to surgery, type of procedure), and total number and intake of relevant **medication** will be documented as well. All variables, except for the quality of life, can be retrospectively collected using the electronic patient record.

### At discharge

The research assistant will monitor the incidence of complications using patient assessment (4AT) and by monitoring the patients record throughout hospitalization, and will assess the outcomes on hospital discharge using patient interview. **Discharge date, medication and mortality** will be evaluated based on the electronic patient record. **Functional status** is measured using the Parker Mobility Score^11^, Barthel Index ^12^, Katz index and Lawton and Brody scale based on reports, if possible from the patient, from next of kin or from nursing staff. **Quality of life** will be evaluated using the EQ-5D questionnaire. **Fall history** will be evaluated using a questionnaire. **Cognition** will be assessed using the Mini-cog test. **Living situation** will be defined within the next 5 categories: living alone at their own home, living with a spouse/partner at their own home, living with children or sibling, living in assisted living facility, living in a facility with 24u care (nursing home, rehabilitation setting,…). Details of care provided will be recorded as one of the following categories: 24h care, daily, irregular, no care. Variables that can be retrospectively collected are as follows: discharge date, medication, mortality, fall history and living situation.

Also **several process outcomes** of the G-COMAN program will be evaluated using registrations in the electronic patient records and by patient interviews: reach of the program (% of eligible patients that were effectively enrolled into the program), fidelity to the program (% of patients included in G-COMAN traumatology program who had a screening or assessment focusing on *delirium, nutritional status, pressure ulcer risk* using a validated tool within 48h of admission to traumatology ward) and specific care process; such as the *time to start physiotherapy*; *time to start dietary advice*; use, *type and duration of fixation;* *use, duration and reason of indwelling catheters (urinary tract catheter or intravenous catheter); medication reconciliation; referral to geriatric day clinic* for follow-up; *and referral to a fracture liaison service (Zoledronate infusion or metabolic bone consultation).*

*Cost-benefit will be calculated by UHL financial division using the UHL cost model based on retrospective data collected at least 3 months post-discharge.*

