### 3.2 Primary endpoints

1) Effectiveness evaluation

- In-hospital complications, including and limited to:

1/ Delirium: on suspicion of delirium the 4AT^9^ will be used to make the diagnosis. Mini-Cog^9^ will be used to assess the cognitive status of the patient

2/ Congestive heart failure: note in the electronic patient record of heart failure

3/ Pneumonia: diagnosis based on imaging or laboratory testing

4/ Deep venous thrombosis or pulmonary embolism: confirmed on imaging

5/ Myocardial infarction: diagnosis stated in the electronic patient record based on clinical image and laboratory testing/ECG findings.

6/ Urinary tract infection based on laboratory testing and needing treatment with antibiotics

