# Statistics

### 8.1 Sample size

Pre- and post-cohort: Sample size calculation was performed based on difference in the risk of complications. In literature a wide variation in complications rates have been reported ranging from 19.9% to 57% in geriatric co-management and from 55% to 71% in the usual care group ^16-18^. Hence, assuming an absolute reduction by 20%, (alfa:= 0.05, power = 0.8, two sided t-test), equal treatment groups and an expected loss of patients of about 5%; a total of 108 patients are needed per group.

Feasibility study: A total of 15 patients receiving the G-COMAN intervention will be recruited for the feasibility study. Approximately 30 healthcare professionals will be recruited for the focus groups and interviews. The total sample of healthcare professionals will be based on the willingness to participate.

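### Delirium, part of the primary endpoint, is sought by 4AT plus record in prospective patients but from the record alone in the retrospective controls, which can attenuate a true benefit

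*Protocol*

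**What the plan says.** Section 3.2 makes in-hospital complications the primary endpoint and lists six items, with delirium first. For delirium it says "on suspicion of delirium the 4AT" is to be used for the diagnosis. The other five rest on record notes, imaging, laboratory results or ECG.

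Section 5.1 (At discharge) describes how complications are found: "The research assistant will monitor the incidence of complications using patient assessment (4AT) and by monitoring the patients record throughout hospitalization". The flowchart in 3.6 gives one schedule for the prospective pre-cohort and the post-cohort. In its separate column for the retrospective pre-cohort, complications are available from the record.

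Section 3.4 explains that the pre-cohort window is too short to reach the sample size and will be topped up: "This results in a pre-cohort that will be partly prospective and partly retrospective". No share is given, and no such supplement is described for the post-cohort.

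Section 8.2 tests the primary outcome between the two groups and does not distinguish the two parts of the pre-cohort. Its closing paragraph on bias names lack of randomisation, death, loss to follow-up and incomplete questionnaires, but not differences in how outcomes are found.

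Section 5.1 (At discharge) also states: "Variables that can be retrospectively collected are as follows: discharge date, medication, mortality, fall history and living situation". Complications are not in that list.

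**The concern.** The less sensitive way of finding delirium occurs only among controls. If charts miss delirium that a research assistant with the 4AT would have found, the observed control rate is too low and the contrast moves against the programme. No adjustment for baseline characteristics in 8.2 removes this, because it is a measurement difference and not a difference in patients. Nor can any later analysis plan supply assessments that were never made.

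Two further features bear on it. The fidelity measure in 5.1 (At discharge) counts delirium screening with a validated tool within 48 hours, so the programme itself may raise detection in the post period. Section 3.4 says outcome assessors are not blinded.

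The internal conflicts matter because they concern the primary endpoint. Read literally, the 5.1 list leaves retrospective controls without it, while 3.6 says they have it. Sections 3.2 and 5.1 leave open whether the 4AT follows suspicion or is applied without a trigger, and that decides how large the detection gap can be.

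**Working it through.** **1. The plan's own figure.** Inputs from 8.1: "alfa:= 0.05, power = 0.8, two sided t-test"; "assuming an absolute reduction by 20" percentage points; "equal treatment groups"; about 5% loss; usual-care complications "from 55% to 71% in the usual care group". The stated result is 108 per group.
- Two-sample t-test with SD 0.5 and difference 0.20: 99 per group; 99/0.95 = 104.2, so 105, within 3% of 108.
- Continuity-corrected proportions, 71% against 51%: 102 per group; 102/0.95 = 107.4, so 108.

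The sample size is not in dispute. It assumes that complications are found equally well in both groups.

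**2. Size of the shortfall.** Let f be the retrospective share of the pre-cohort, d the delirium risk, o the risk of any other complication (taken as independent of delirium), 0.9 the detection with 4AT plus record, and s the detection from the record alone. The protocol gives none of these; all are assumptions. With no true effect:

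observed rate, prospective = 1 − (1 − 0.9d)(1 − o)

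excess in the post-cohort = f(1 − o)d(0.9 − s)

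On f: 4.3 gives about six months of prospective pre-cohort inclusion (October 2021 to March 2022) and about twelve for the post-cohort. With similar accrual and equal targets, f = 0.5 is plausible.

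*Other complications at 30%, f = 0.5:*
- d = 0.25, s = 0.6: 0.5 × 0.70 × 0.25 × 0.3 = 2.6 points
- d = 0.35, s = 0.4: 0.5 × 0.70 × 0.35 × 0.5 = 6.1 points

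These inputs give a prospective composite of 1 − 0.775 × 0.70 = 46% to 1 − 0.685 × 0.70 = 52%, below the 55-71% in 8.1.

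*Other complications set so that the prospective composite is 55% to 71%, f = 0.5.* Here 1 − o = (1 − composite)/(1 − 0.9d):
- Smallest: d = 0.25, composite 71%: 1 − o = 0.29/0.775 = 0.374; with s = 0.6, 0.5 × 0.374 × 0.25 × 0.3 = 1.4 points
- Largest: d = 0.35, composite 55%: 1 − o = 0.45/0.685 = 0.657; with s = 0.4, 0.5 × 0.657 × 0.35 × 0.5 = 5.7 points

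Taken together, the range is about 1.4 to 6 points, or 7% to 30% of the 20-point target. The result is proportional to f: for f from 0.25 to 0.75 the calibrated range is 0.7 to 8.6 points, and the range with o = 30% is 1.3 to 9.2.

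**3. If the 4AT is used only on suspicion.** The excess is also proportional to the detection gap. With a gap of 10 points instead of 30 to 50 (f = 0.5, o = 30%), it is 0.5 × 0.70 × 0.25 × 0.1 = 0.9 to 0.5 × 0.70 × 0.35 × 0.1 = 1.2 points.

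**4. Effect on power.** True rates are taken as 60% and 40%, with 102 evaluable per group (108 × 0.95 = 102.6). Only the control rate is lowered.

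| Shortfall in control rate | Observed difference | Power |
|---|---|---|
| 0 points | 20.0 | 82% |
| 1.5 | 18.5 | 76% |
| 3 | 17.0 | 68% |
| 4.5 | 15.5 | 60% |
| 6 | 14.0 | 52% |

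**The case against.** Much can be said for the plan. The prospective pre-cohort and the post-cohort follow the same schedule. Five of the six components come from record, imaging, laboratory or ECG findings that any chart can supply. Section 3.2 ties the 4AT to suspicion, and suspicion may itself be charted. Section 3.4 notes that hospital-wide delirium protocols exist under usual care. If delirium and other complications cluster, a missed delirium changes the any-complication status less often than independence implies. The bias from chart review is also conservative: it works against a false claim of benefit. All of this stands. It confines the problem to delirium in part of one group and makes the size uncertain, but it does not remove the difference.

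Several stronger readings are tempting and are not supported. A reader might infer daily 4AT testing, but 5.1 says only that monitoring runs through the hospital stay. A reader might infer that a null result could be wholly an artefact of measurement, but the calculations at a half share show attenuation and lost power, not the erasure of a 20-point effect. A reader might count the DOS follow-up in 3.3 as raising detection, but it applies only once a patient is delirious. Finally, the lack of a data-source term or sensitivity analysis in 8.2 is not in itself an error, since a statistical analysis plan that is not shown may contain one.

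**Conclusion.** The point holds for delirium. Its ascertainment differs between the retrospective controls and everyone else, the difference falls on one side of the primary comparison, and the stated analysis compares pooled groups. The direction from chart under-recording is towards hiding a benefit. The size cannot be derived from the protocol. Roughly 1.4 to 6 points is an illustration that rests on an assumed half share, assumed delirium risk, assumed detection rates and independence of components. It is about 1 point if the 4AT adds little to what is charted. The existence of the difference and the two textual conflicts (3.6 against the 5.1 list; 3.2 against 5.1 on the 4AT) are certain. This should be fixed, but it does not invalidate the design.

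**What to change.** - Abstract complications from the record with one checklist for all patients in both cohorts. Record separately any delirium found only by the study's 4AT, so that such results do not enter the record-only definition.
- Beside the primary analysis, pre-specify (a) a record-only comparison of all patients, (b) prospective pre-cohort against post-cohort using 4AT plus record, and (c) the composite without delirium. Base the conclusion on whether these agree.
- State the retrospective share of the pre-cohort, and name differential ascertainment among the biases at the end of 8.2.
- Add complications to the list of retrospectively collected variables in 5.1 (At discharge), and reconcile 3.2 with 5.1 on when the 4AT is done.

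The cost is small. Record abstraction is already planned and no new patient contact is needed. Patients already enrolled may need their charts re-read if the source of a delirium diagnosis was not kept. Comparison (a) is less sensitive for delirium and does not remove any rise in documentation caused by the programme, which is why (c) is needed. Comparison (b) has fewer patients and less power. Making record-only abstraction the primary definition would be a larger step with its own trade-offs, and it is not required here.
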